## Abstract

**Introduction:**

Decentering describes the ability to voluntarily adopt an objective self-perspective from which to notice internal, typically distressing, stressors (eg, difficult thoughts, memories and feelings). The reinforcement of this skill may be an active ingredient through which different psychological interventions accrue reductions in anxiety and/or depression. However, it is unclear if decentering can be selectively trained at a young age and if this might reduce psychological distress. The aim of the current trial is to address this research gap.

**Methods and analysis:**

Adolescents, recruited from schools in the UK and Ireland (n=57 per group, age range=16–19 years), will be randomised to complete 5 weeks of decentering training, or an active control group that will take part in a combination of light physical exercise and cognitive training. The coprimary training outcomes include a self-reported decentering inventory (ie, the Experiences Questionnaire) and the momentary use of decentering in response to psychological stressors, using experience sampling. The secondary mental health outcomes will include self-reported inventories of depression and anxiety symptoms, as well as psychological well-being. Initial statistical analysis will use between-group analysis of covariance to estimate the effect of training condition on self-rated inventories, adjusted for baseline scores. Additionally, experience sampling data will be examined using hierarchical linear models.

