## Methods

### Study design

The design is a randomised controlled feasibility trial (comparing a psychological decentering training to an active control programme) with school aged adolescents (aged 16–19 years). The study will run from December 2021 until July 2022, split into several cohorts. Self-rated inventories of training and mental health outcomes will be assessed at three time points: within 1 week prior to the start of programme (baseline); within the third week of training (mid-intervention); and 1 week after the programme has finished (postintervention).

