### Sample size

The primary training outcome is self-rated decentering and this will be assessed using both a popular inventory of decentering (Experiences Questionnaire; EQ^8^) and ESM items. There is no consensus on how to best conduct a statistical power analysis for ESM data. Power and sample calculations were therefore based on the effect of training condition on EQ scores. A power analysis calculated in G*Power indicated that a total sample size of 90 is powered at 80% to observe a significant effect of training condition (decentering vs control) on postintervention decentering with a medium effect size of f=0.3 (α=0.05) after adjusting for baseline EQ score. A medium effect size is plausible given that previous research reports a medium–large effect of extant psychological intervention on EQ scores. An attrition rate of around 20% is anticipated based on our previous research. Therefore, with 57 participants in each group, the current study is adequately powered to observe a medium to large effect of decentering training on our candidate training outcome measures and to determine the nature of this interaction. Regarding our secondary mental health outcomes (ie, anxiety, depression and psychological well-being), a sample size of 57 per group is consistent with our previous research to evaluate the impact of novel psychological interventions. That is, such group sizes can provide a reasonable range of point estimates of the effect on mental health outcome measures that are sufficient to guide later research; for example, 57 participants per group is powered at 88% to observe a significant (p<0.05) main effect of group (decentering vs active control) on baseline adjusted mental health outcomes with an effect size f=0.26.

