#### Decentering outcome measures

The primary training outcome measure is self-rated decentering as measured using the EQ. A secondary decentering outcome measure is the self-rated use of psychological decentering in response to psychological stressors as measured using ESM. These measures have been included to address research questions 1a and 1b, respectively.

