#### Consent and data collection

Recruited volunteers will complete an eligibility check during an initial phone call. Volunteers who are eligible will be invited to participate in the study. Written informed consent will be sought after an initial briefing that explains the data collection protocol (see online supplemental appendix B for consent form). This briefing will also include a tutorial on downloading and using the experience sampling app (PsyMate2; www.psymate.eu). Participants will also have the opportunity to ask any questions. To discourage possible contamination, participants will be asked to keep the content of the study confidential from others. Once consent is provided, participants will be given an anonymous trial identification code and added to an encrypted list for allocation. Participants will also receive a URL link to complete baseline measures. Figure 1 illustrates the full schedule for outcome measures. Participants will receive a tutorial on accessing the intervention materials.

10.1136/bmjopen-2021-056864.supp4Supplementary data

Over 5 weeks, participants in both interventions will access and rehearse exercises (Monday–Friday). Decentering training exercises are based on audio files to be delivered via their preferred music/poststreaming services (eg, Spotify/Podcast Addict). The active control exercises are based on YouTube videos posted on a Private Channel. Each day, the PsyMate2 App will prompt participants to complete their daily exercise as well as complete any required ESM items. These will be sent four times per day. A brief survey will also be sent through email each evening to ask whether participants completed their daily exercises, and if so, to ask about their experiences as well as questions on their mood states. At the end of week 5, participants will be asked to complete the online assessment battery. Participants will then complete a debriefing session. During the debriefing session, they will be given the opportunity to provide feedback on their experience of the study, and to ask any questions they may have. They will also be given a list of relevant mental health resources should they feel the need to access them.

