#### Statistical analysis

##### Self-rated and performance-based measures

The statistical analysis will be conducted by the trial statistician (PW) who will be blind to training condition. The analysis will be conducted on an intention-to-treat basis and a similar initial analysis is planned for (1) the primary training outcome (ie, self-rated EQ scores) and (2) secondary mental health outcomes (ie, CES-D, RCADS, STAXI-2, SDQ and WEMWBS). Analysis of covariance will be calculated to estimate the effect of training condition on outcome measures after adjusting for baseline performance and grouping stratification variables. This model will be calculated for our primary end-point, that is, post intervention (ie, postintervention outcome adjusted for baseline score). This model will additionally be calculated for our mid-intervention time point (ie, mid-intervention outcome adjusted for baseline score) and post intervention. There are no planned interim analyses. If a subset of items of a measure (<20% within-measure missing data), a total score will be calculated using the mean score across the non-missing items; an approach we have reported elsewhere (www.osf.io/d6y9q). Otherwise, the score for that measure will be noted as missing. We will assume that data will be missing at random and address this using standard imputation approaches in R (R Core Team, 2013).

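### ESM decentering is coprimary in the abstract but secondary in the outcomes section, so the stated 5% and 80% describe the primary claim only if EQ is the sole primary outcome; the post-intervention time point also conflicts

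*Protocol article*

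**What the plan says.** **Status of ESM decentering**

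- Abstract, Methods and analysis: "The coprimary training outcomes include a self-reported decentering inventory (ie, the Experiences Questionnaire) and the momentary use of decentering", the second by experience sampling.
- Current study objectives: momentary decentering by ESM sits under the primary aim, as question 1b.
- Sample size: "The primary training outcome is self-rated decentering and this will be assessed using both a popular inventory of decentering" (the EQ) and ESM items. The section then says that power was calculated for EQ only, because there is no agreed method for ESM data. It concludes that 57 per group is adequate for the training outcome measures, in the plural.
- Decentering outcome measures: "The primary training outcome measure is self-rated decentering as measured using the EQ". Then: "A secondary decentering outcome measure is the self-rated use of psychological decentering in response to psychological stressors as measured using ESM".
- Self-rated and performance-based measures (statistical analysis): "the primary training outcome (ie, self-rated EQ scores"), with post intervention as the primary end-point. ESM is not mentioned here; it has its own analysis section.

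**Time of the post-intervention assessment**

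- Study design: "1 week after the programme has finished (postintervention").
- Consent and data collection: "At the end of week 5, participants will be asked to complete the online assessment battery".

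**The concern.** One outcome carries two incompatible labels, and the label decides which result supports the primary claim. With a null EQ and a significant ESM result, the trial could be reported as positive by citing the abstract and the Sample size section, or as negative by citing the outcomes and analysis sections. The statistician's blinding does not prevent this, because the label can still be chosen when the results are written up after unblinding.

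Under the coprimary reading, the article does not say whether one or both outcomes must succeed. The two rules have different operating characteristics, and neither was used in the sample size calculation.

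The timing conflict concerns the time point that the analysis section makes primary. An assessment at the end of the week 5 revision period captures the response as training closes. One a week later captures what remains after a week without scheduled training. For the CES-D, a secondary outcome that asks about the past week, the two timings also cover different weeks.

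**Working it through.** **1. Reproduce the plan's figure (EQ as sole primary).** Inputs from Sample size: f = 0.3 (d = 0.6 for two equal groups), alpha 0.05, one baseline covariate, total N = 90, about 20% attrition. The F test is taken as non-directional.

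- Power = P(F' > F crit), with F' noncentral F, df1 = 1, df2 = N − 2 − 1 = 87, λ = f²N = 0.09 × 90 = 8.1.
- Result: 80.4%. N = 90 is the smallest total that reaches 80%, as stated.
- Attrition: 90 / (1 − 0.20) = 112.5, so 113, or 114 for equal groups (57 each). In reverse, 114 × 0.8 = 91.2; power at 91 is 80.8%.

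The sample size is right for the EQ test, whatever the status of ESM.

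**2. ESM coprimary, either outcome suffices, no adjustment.** Familywise error = 1 − P(|Z1| < 1.96, |Z2| < 1.96), bivariate normal. The document gives no correlation between the two test statistics, so a range is shown.

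| Correlation | Familywise error |
|---|---|
| 0 | 1 − 0.95² = 9.75% |
| 0.5 | 9.1% |
| 0.7 | 8.3% |
| 0.9 | 7.0% |

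Power for EQ alone is unchanged here. If alpha were split at 0.025 each, EQ power at N = 90 would be 71.3%. Regaining 80% would need 109 analysed; 109 / 0.8 = 136.25, so 137 randomised, or 138 for equal groups.

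**3. ESM coprimary, both must succeed.** The type I error of the joint claim is at most 5%, because each test is held at 0.05. Joint power needs a power for ESM, which the document does not give. As an assumption, ESM is given the same 80.4% as EQ.

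| Correlation | Joint power |
|---|---|
| 0 | 0.8036² = 64.6% |
| 0.5 | 69.2% |
| 0.7 | 71.8% |
| 0.9 | 75.4% |

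If ESM power were lower than assumed, joint power would be lower too.

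**4. Which reading fits the rest of the plan.** The primary end-point is post intervention. ESM items are delivered only in the baseline period and the five training weeks, and are analysed as linear growth across the intervention. ESM decentering therefore has no post-intervention value. EQ as sole primary fits the outcomes section, the analysis section and the power calculation; the coprimary reading does not fit them.

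**5. Timing.** There is one post-intervention battery and one EQ test at it. Moving it by a week leaves steps 1 to 3 unchanged and alters only which effect is estimated.

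**The case against.** The strongest reply is that the error rate and power are stated for one test only, the EQ comparison, and that the article says so openly. This stands. A reader might infer that the stated 5% and 80% are wrong, or that both fail once ESM is coprimary. The document supports neither. The figures reproduce, and no single coprimary rule breaks both: the either-outcome rule raises error and leaves EQ power at 80%, while the both-outcomes rule lowers joint power and keeps error at or below 5%. It would also be too strong to say without qualification that the error rate nearly doubles. That fits low to moderate correlation, and at 0.9 it is 7.0%.

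Other replies stand in part:

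- Only the outcomes section actually labels ESM decentering secondary. The analysis section names EQ as primary without mentioning ESM.
- The Sample size section describes one construct measured two ways and does not use the word coprimary. Its overreach lies in the plural claim of adequate power.
- A further multiplicity problem from testing the two ESM distancing items separately might be inferred, but the ESM analysis section does not plan this.
- On timing, exercises run Monday to Friday, so the end of week 5 may already follow the last exercise. The schedule figure, not shown here, may be clearer. The texts still differ by about a week. A reader might take the timing conflict as further damage to alpha or power; it affects neither.
- A success rule or alpha split may sit in an analysis plan that is not shown, and this is a feasibility trial. Its absence is therefore not the finding. Opposite labels for the same outcome are, and an analysis plan does not remove them from this document.

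**Conclusion.** Wrong as written. ESM decentering is coprimary in the abstract and part of the primary outcome in the Sample size section, but secondary in the outcomes section, while the analysis section names EQ alone as primary. The alpha of 0.05 and 80% power are correct for EQ, and they characterise the trial's primary claim only if EQ is the sole primary outcome. With ESM coprimary, the consequence is either a familywise error of about 7.0% to 9.75% (either suffices, unadjusted) or a joint power of about 65% to 75% (both required), over correlations of 0.9 to 0 for the error and 0 to 0.9 for the power. The correlations are assumed, and the power range also assumes 80% power for ESM. The claim of adequate power for several training outcome measures is supported for EQ only.

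The conflict over the post-intervention time point is a separate fault. It leaves the primary effect undefined as to time, without changing alpha or calculated power.

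**What to change.** Give ESM decentering one status throughout. The simplest choice, consistent with the outcomes section, the analysis section and the power calculation, is EQ at post-intervention as the single primary outcome and ESM decentering as secondary. That means:

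- removing the word coprimary from the abstract;
- in Sample size, correcting the statement that the primary outcome is assessed by both measures, and limiting the power claim to EQ.

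If coprimary status is kept instead, state whether one or both outcomes must succeed, and give the alpha and power that follow.

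Reconcile Study design with Consent and data collection so that there is one post-intervention assessment window, the same for both arms and all cohorts.

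The single-primary choice costs a wording amendment and a registry update, with no extra participants or data. Its downside is that the ESM result can no longer carry a primary claim. Keeping coprimary status may cost more: with alpha split equally, for example, 80% power on EQ needs 138 randomised instead of 114.

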**Ethics and dissemination:**

This study was approved by the Cambridge Psychology Research Ethics Committee, University of Cambridge (PRE.2019.109). Findings will be disseminated through typical academic routes including poster/paper presentations at (inter)national conferences, academic institutes and through publication in peer-reviewed journals.

**Trial registration number:**

ISRCTN14329613.

Strengths and limitations of this studyWe aim to strengthen an active and pan-therapeutic skill that features across different psychological interventions, and may improve well-being in adolescents at high risk of mental health difficulty.The intervention will be highly accessible by capitalising on extant social media and streaming services.Ecological momentary assessment will facilitate a temporally sensitive investigation into the effects of decentering training in everyday life.A lack of face-to-face interaction between experimenters and participants may undermine adherence.The study may be demanding as it requires daily, although brief, engagement over a several weeks.

## Introduction

### Background

Anxiety and depression are a considerable public health challenge. Since these difficulties often begin before the age of 24, responding to this challenge requires a special focus on adolescence.^1^ It has been suggested that an effective way to promote early mental health is through universal approaches^2–4^; these are interventions that can be offered across a broad community of young people, irrespective of symptom severity. The goal of such universal approaches is to not only reduce distress in young people experiencing symptoms, but also to prevent future anxiety and depression onset in those who may be asymptomatic. However, their effectiveness depends on how well an intervention focuses on psychological experiences and mechanisms that are relevant across the entire spectrum of mental health, from risk to resilience and through to flourishing. One strategy is therefore to target widely relevant therapeutic skills that can help manage distressing inner experiences (eg, unpleasant feelings, thoughts, memories), which can otherwise trigger short-term distress and long-term risk of anxiety and depression onset. Psychological decentering, or decentering for short, may be one such skill.

Psychological decentering is a key concept within psychological therapy and science.^5^ It is characterised as an adaptive self-observation style wherein one can attend to, not just the mental content of distressing inner experiences, but also its underlying cognitive nature.^6 7^ Thus, decentering relates to how a person interacts with the difficult inner events prompted by experiences in daily life—it involves the ability to generate an objective self-perspective wherein one can notice mental experiences as imperfect models of the real-world rather than precise reflections. For example, a person might notice ‘I am thinking I am depressed right now’ instead of only noticing and then believing the thought ‘I am depressed’.^8^ Decentering resultantly restricts the disproportionate influence psychological stressors may have on affect, behaviour and sense-of-self. Indeed, brief therapeutic exercises that stimulate a decentred self-perspective have been shown to reduce negative emotional reactivity towards stressors like unpleasant memories and negative self-relevant statements.^9–13^ Evidence also indicates self-reported decentering traits in adolescence are associated with fewer overall symptoms of anxiety and depression.^14–17^

Decentering is a malleable skill that can be refined through psychological intervention.^7^ Medium-to-large changes in self-reported decentering are reported in adults experiencing anxiety and depression following a range of psychological interventions. This includes cognitive behavioural therapy,^18 19^ acceptance-based approaches^20–22^ and mindfulness training.^23–25^ In fact, emerging evidence suggests that intervention-related increases in decentering are a common pathway through which different psychological interventions deliver reductions in anxiety and depression.^21 26 27^ This has encouraged some investigations into whether or not decentering can be trained selectively so to improve mental health. For example, Travers-Hill *et al* trained adults with a diagnosis of recurrent depression currently in remission but experiencing residual depression symptoms to practice self-distancing techniques in response to difficult autobiographical memories.^28^ This resulted in a significant increase in self-reported measures of decentering relative to an active comparison group who learnt strategies to manage maladaptive avoidance tendencies. Additionally, those who learnt to apply this decentering-related technique reported less distress towards negative memories at post intervention even in the absence of instructions to self-distance.

Therapeutic exercises that target decentering skills are already nested within different psychological interventions.^7^ Emerging evidence also indicates that these components can be delivered in isolation so as to selectively boost decentering and reduce risk of relapse in formerly depressed adults.^28^ However, a remaining question is ‘can decentering skills be selectively reinforced during adolescence, and if so, through what therapeutic techniques?’ This is the primary research question guiding the current study. It is also unclear if boosting adolescent decentering skills might impact on emotion and mental health. The current study will therefore evaluate, as a secondary question, how decentering training impacts anxiety, depression and emotional reactivity in adolescence. This information will inform future research trials and ultimately help in the investigation of effective universal approaches in youth mental health. A straightforward way to address these questions might be to examine the impact of decentering training on trait-level measures of decentering and symptom severity at critical time points, for example, pre and postintervention design. However, this approach lacks the sensitivity required to detect subtle changes in decentering in response to momentary psychological stressors and their impact on emotion. A design that also includes ecological momentary assessment or experience sampling methods (ESM) could therefore facilitate a more ecological investigation of the use of decentering in everyday life as well as its impact on transient psychological stressors and emotional states.

### Current study objectives

The primary aim of the current study is to investigate if decentering can be improved during adolescence via an intensive decentering training programme. This will be investigated (1a) at a trait level by examining changes in self-reported experience of decentering (via a standard decentering inventory) and (1b) at a situational level by examining self-reported use of decentering skills in response to momentary psychological stressors (via ESM assessments). Here, repeated measures of participants’ negative emotional reactivity towards momentary inner experiences (eg, feelings, thoughts and memories) will be recorded across the duration of the intervention. A secondary aim is to explore potential mental health outcomes associated with reinforced decentering skills. This will be investigated (2a) at the symptom level by examining relative change in self-rated anxiety, depression and psychological well-being and (2b) at the situational level by recording emotional reactivity towards momentary psychological stressors using ESM. A final exploratory aim is to investigate some of the cognitive correlates of decentering and training. Thus, this study will answer the following research questions: (1a) Is decentering training during adolescence associated with increased decentering reports relative to an active control condition? (1b) Is decentering training during adolescence associated with increased decentering in response to negative mental events relative to an active control condition? (2a) What is the impact of decentering training on youth mental health relative to an active control condition? (2b) What is the impact of decentering training on emotional reactivity towards momentary negative mental events relative to an active control? (3) What are the cognitive correlates of decentering training during adolescence?

This study will address these research questions in a cohort of adolescents who are at increased risk of depression. This is a first step towards our long-term goal to develop a universal intervention that targets psychological experiences and mechanisms that are broadly relevant in young people. Adolescents experiencing elevated symptoms of depression will be recruited from both the UK (eg, sixth form colleges) and Ireland (eg, secondary level education high schools) and will be randomly assigned to a 5-week decentering training programme or an active control. Both programmes will be delivered remotely via extant social media platforms; this means they can be delivered at low cost, are easily accessible and are flexible regarding other commitments of our participants. The decentering intervention comprises 10–15 min of audio exercises to be made available each weekday through music/podcast streaming services, for example, *Spotify*, *iTunes*, *Deezer*, *Podcast Addict*. Participants will practice a specific decentering technique each week, which has been adapted from either the literature or an extant psychological therapy. Participants will also practice brief mindfulness-based grounding exercises each week to encourage the monitoring of inner experiences like emotional thoughts, memories and feelings. The overall goal of this programme is therefore to teach adolescents different ways to generate an objective self-perspective from which they can interact with negative psychological events encountered in daily life. Rather than rehearsing decentering techniques, the active control condition comprises 10–15 min of gamified cognitive tasks for completion on a personal smartphone. In addition, participants in this condition will be given short physical movement routines to complete in lieu of mindfulness-based grounding.

